### Cost-effectiveness analysis

For our analysis, both a hospital and a societal perspective will be used. Because the surgical treatments to be analyzed do not differ in their DRG-codes, the costs for the hospital will be estimated based on differences in costs of implants used for the surgery and length of hospital stay. Cost-benefit is then expressed as cost per reduced length of stay.

For the societal perspective, additional resource utilization after discharge from hospital will be assessed based on a patient diary. After being discharged from the hospital, the patient will report direct medical costs such as those from physiotherapy, visits to general practitioners or specialists, and surgery-related medication (e.g., analgesics). Additionally, indirect costs from work absences will be recorded. For data on efficacy, quality-adjusted life years (QALY) are estimated by using the SF-36^® ^Health Survey, a generic outcome measure designed to examine a person's perceived health status. An incremental cost-effectiveness ratio in terms of costs per QALY will be calculated.

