The concept is to maintain or restore intervertebral motion in a controlled fashion, whether by restricting extremes of spinal movement or by dampening the kinetic energy involved in motion. The goal of these implantable devices is to mimic the behavior of the healthy spinal column [6,7]. Companies have developed various types of flexible pedicle screw systems (e.g. Surgicraft's Graf ligament, Bioflex's Spring rod, Dynesys^®^, AccuFlex™, Medtronic's Peek rod, Isobar^®^) and topping off systems (e.g. DTO™, DSS™, CosmicMIA™). Topping off has been reported to provide dynamic stabilization along with a consequent reduction of degeneration in the adjacent segment [8,9]. Maserati et al. performed a retrospective analysis of a population after undergoing the topping off procedure. They concluded it was a promising alternative for multilevel fusion with the potential to avert ASD [10]. However, in a recently published, prospective, randomized clinical trial of 60 patients comparing fusion with a hybrid system device versus conventional fusion over 6 years of follow-up, clinical results did not differ between the groups (ODI, VAS, satisfaction). Although the hybrid fixation showed less progression of degeneration in the adjacent segment, there was a higher rate of implant failure. This study group did not recommend prophylactic dynamic stabilization [11]. Overall, to date there is no convincing evidence that these systems provide any clinical benefit whatsoever.

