#### Secondary Outcome Measures

1. Total, MCS, and 8 individual dimensions and subscales of the SF-36™ (version 4.0) for confirmation and clarification of the primary outcome results.

2. ODI (cross-cultural adaption of the ODI version 2.1 for use with German-speaking patients)[24]: this is one of the condition-specific questionnaires recommended for use with back pain patients. The ODI is a standardized, patient-completed questionnaire which gives a subjective percentage score of level of function (disability) in activities of daily living for those rehabilitating from low back pain. The questionnaire examines perceived level of disability in 10 everyday activities of daily living.

3. COMI questionnaire (version 2008): a patient-oriented, short, multidimensional outcome instrument validated for patients with spinal disorders.

4. X-rays will be taken after 6 weeks, 6, 12, 24, and 36 months. Further assessments will be performed annually. These are common intervals after surgical implant procedures not requiring extraneous radiation. At the point in time where adjacent instability is identified radiographically, we will reevaluate and compare the clinical outcome. Criteria for radiologic ASD as well as adjacent instability are listed in the appendix (definition of radiologic instability and Weiner's classification). Pre- and postoperative x-rays must be compared to assess the Weiner's classification score. X-rays will be evaluated by experienced radiologists.

5. Clinical ASD will be assessed (see appendix for the definition).

6. Work-related function/disability at the time of surgery and after surgery, plus the duration until return to work. At each visit, patients will be interviewed about their level of work-related function/disability as well as the time point when/if they return to employment.

7. Inpatient mortality and mortality at 6 months.

8. Surgery-related data (blood loss, length of incision, duration of surgery) are taken from the surgical report.

9. Intraoperative and postoperative complication rates (e.g. implant failure)

10. Adverse events (AE) and serious adverse events (SAE) will be documented and monitored throughout the study.

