## Discussion

New hybrid systems might improve the outcome of lumbar spine fusion. To date, however there is no convincing published data regarding these topping off systems. High quality data is required to provide a preliminary impression of the advantages and disadvantages of such devices. If only because topping off devices are quite expensive compared to conventional implants, nonessential use should be avoided. In fact, these high costs necessitate efforts by health care providers to examine the effects of these implants. Randomized clinical trials are highly recommended to evaluate the benefits or harm to patients.

In the intervention group, the approach to the spine will be enlarged compared to that of the monosegmental fusion group. The longer approach itself could bring about a negative outcome compared to that of regular fusion (e.g., due to muscle damage, blood loss, higher risk of infection). As well, implant failure rates can be compared between the groups. The crucial question, however, is the ability to prevent ASD.

Placebo is not an acceptable option for the control group for fundamentally ethical reasons. Not only would such an option deprive the patient of adequate treatment, but also to have a realistic placebo would require an invasive procedure without the implantation of a medical device, thus exposing him/her to significant risks without providing benefit. Furthermore, a "placebo device" as replacement for the respective topping-off system does not exist.

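### Hospital cost omits theatre time although duration of surgery is recorded, which probably understates hybrid cost; reoperation is also outside the hospital list, with unknown direction

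*Protocol article*

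**What the plan says.** The Cost-effectiveness analysis section takes a hospital and a societal perspective.

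- **Hospital.** The section gives a reason, "Because the surgical treatments to be analyzed do not differ in their DRG-codes", and then the rule: "the costs for the hospital will be estimated based on differences in costs of implants used for the surgery and length of hospital stay". No wording marks these two items as examples. The result is a ratio: "Cost-benefit is then expressed as cost per reduced length of stay".
- **Societal.** Resource use after the patient has left hospital is added from a diary, in which "the patient will report direct medical costs such as those from physiotherapy, visits to general practitioners or specialists, and surgery-related medication (e.g., analgesics"). This list is open. Work absence is added as an indirect cost, and the result is an incremental cost per QALY.

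Elsewhere, item 8 of the Secondary Outcome Measures states: "Surgery-related data (blood loss, length of incision, duration of surgery) are taken from the surgical report". Item 9 covers complication rates, with implant failure as its example, and item 10 covers adverse and serious adverse events. The Interventions sections describe the hybrid operation as the control operation (PLIF) plus a flexible pedicle screw system above the fusion. The Discussion says of the hybrid arm that "the approach to the spine will be enlarged compared to that of the monosegmental fusion group".

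**The concern.** The DRG argument does not support the two-item rule. If both arms are reimbursed alike, revenue cancels out of the hospital's comparison, and what remains is the difference in resources used. Theatre time is one of those resources, and the two operations differ in extent by design. A cost comparison that counts the extra implant but not the time needed to place it describes only part of the difference.

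The gap is not confined to the hospital ratio. The societal total adds only what happens after discharge, so theatre use during the index operation enters neither perspective and is missing from the cost per QALY too.

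Readmission and reoperation raise a second question. Implant failure and adjacent segment disease are the harm and the benefit that the Objective section asks about. The hospital list leaves out the inpatient cost of treating either after the index stay, and the societal list does not name it. The Discussion gives the high price of these devices as a reason to study them, so the cost result will be read with attention even though it is not the primary outcome.

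**Working it through.** The cost section states no figure, so there is none to reproduce. The article gives no unit cost, operating time or reoperation rate. The check therefore concerns which items are counted, and the sign of what is left out.

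**1. Where each item is counted**

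| Item | Recorded in the trial | Hospital cost | Societal cost |
|---|---|---|---|
| Implants | yes | yes | carried over |
| Length of stay | yes | yes | carried over |
| Index theatre time | yes, item 8 | no | no, it precedes discharge |
| Readmission, reoperation | not named; related events under items 9 and 10 | no | not named, not excluded |

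**2. The omitted difference**, hybrid minus control, per patient:

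omitted = T + R × (a − b)

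Here T is the extra theatre cost, R the cost of one reoperation, a the excess risk of implant-related reoperation with the hybrid, and b the risk of adjacent-segment reoperation that the hybrid averts. A positive value means that the plan understates hybrid cost.

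**3. Theatre term.** T is zero or positive whenever hybrid surgery takes at least as long as PLIF alone. The article does not state operating times. That hybrid surgery takes longer is an inference from the added screw system and the larger approach.

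**4. Reoperation term.** In Background, the report of the earlier randomised trial of 60 patients points both ways. It says that "there was a higher rate of implant failure" with hybrid fixation, and the same sentence reports slower deterioration of the neighbouring level. Averting adjacent segment disease is the purpose of the device, and Background cites a cohort in which 16.5% had it at five years. So a and b may both be above zero, and the article gives neither.

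**5. Sign check on assumed values**, in arbitrary cost units: R = 10,000; T from 0 to 1,000; a from 0 to 0.10; b from 0 to 0.165. The top value of b is extreme, since it supposes that every case in the cited five-year rate would be reoperated and that the hybrid averts them all.

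- Lowest: 0 + 10,000 × (0 − 0.165) = −1,650
- Highest: 1,000 + 10,000 × (0.10 − 0) = +2,000
- With T = 500 and a = 0.05, the sign turns where 500 + 10,000 × (0.05 − b) = 0, that is at b = 0.10
- Theatre term alone (a = b = 0): 0 to +1,000, never negative

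These inputs are not estimates. They show only that the theatre omission has one likely direction, while the total including reoperation can have either sign.

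**The case against.** Several points can be made for the plan.

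- **The main known difference is counted.** The dearer implant is in the hospital list, and complications that prolong the index admission enter through length of stay. This stands and limits the size of the gap. It does not cover theatre minutes, which days in hospital do not measure.
- **An article condenses the economic plan.** Unit prices and detailed components may well be in a fuller document. Here, though, the article states a rule and a reason for it, and the reason does not justify the rule. That is a stated choice, not a missing detail.
- **The societal list is open.** A readmission after discharge can be recorded in the diary and priced by the analyst. This stands: reoperation cannot be called excluded from the societal perspective, only unnamed. It does not help with index theatre time.
- **The analysis is peripheral.** Cost-effectiveness is not among the ten numbered secondary outcomes, the target is 30 patients, and the PCS result is untouched. This stands and bears on priority.

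A reader might go further and infer that reoperation falls more on the hybrid arm, so that the cost comparison as a whole favours the device. The documents do not support this. No reoperation rate is given, and the evidence on implant failure comes in the same sentence as evidence pointing the other way. Nor does the article predict more blood loss or infection: only the larger approach is stated as certain, and those consequences are named as possibilities.

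**Conclusion.** The point holds for theatre time. The hospital perspective omits it on a ground that concerns reimbursement rather than resource use, although duration of surgery is recorded, and the diary cannot recover it for the cost per QALY. The omission probably understates hybrid cost. That rests on the inference that added instrumentation through a larger approach takes longer, and on the assumption that the daily rate used for length of stay does not already include theatre cost. The amount cannot be computed from the article, and any effect in money per QALY would rest wholly on invented inputs.

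For readmission and reoperation, the finding is only that the hospital list leaves them out and the societal list does not name them. The net direction is unknown, and so is the direction of bias in the comparison as a whole. The change is worth making because it corrects a stated method at little cost. It concerns a supporting analysis, not the trial's main conclusion.

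**What to change.** 1. Add index theatre time to the hospital cost, as recorded duration of surgery times a hospital unit cost per minute, and carry it into the societal total. State that the daily rate for length of stay excludes theatre cost, so that nothing is counted twice.
2. Cost readmissions and reoperations of any cause in both perspectives, over a stated follow-up period, and report implant-related and adjacent-segment-related events separately so that both directions can be seen.
3. Identify these events from the complication and serious adverse event records together with the diary. Hospital records alone could miss care given elsewhere.
4. Drop the equal DRG code as the reason for limiting the cost items.

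Duration of surgery, complications and serious adverse events are already collected. What is needed is revised wording, unit costs from hospital accounts and, if the forms do not already capture it, a clear entry for readmission and reoperation. The downside is a little more costing work.

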### Intervention group - hybrid system

The intervention group will receive a hybrid system with PLIF and a flexible pedicle screw system above the fusion. Surgery will be performed using the following devices: Optima ZS™+ DTO™ (Zimmer^® ^Spine Germany GmbH, Kiel, Germany), Wave^© ^Lumbar Cage (Advanced Medical Technologies AG, Nonnweiler, Germany)

Only skilled spine surgeons (with minimum experience of 30 fusion procedures) will participate in the trial. Intraoperative photo documentation will assist in preventing variations of the procedure (e.g., enlargement of decompression/approach). We will also provide an instructional movie on the procedural standards as well as evaluation of the x-rays.

All patients will receive a surgical drain, to be removed 2 days post-surgery. Both groups of patients will receive physical therapy, beginning on the day after surgery. Patients will be discharged only after sufficient convalescence with unremarkable wound healing. Hospital admission lasting 8-10 days will be necessary. Physical therapy will be performed during the inpatient period. After hospital discharge, physical therapy will be continued under outpatient conditions. This therapy will not be standardized in order to reflect reality.

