### Sample size

Our target recruitment is 30 patients. We assume a loss of follow-up of 10%, so that 27 patients should be available for the final analysis. The normalized form of the SF-36™ PCS (mean 50, standard deviation 10) is assumed. With this number of patients, using a two-sided t-test, a normalized PCS score difference of 11.2 or more could be detected with a power of 80% and alpha = 0.05.

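### The hospital economic result is fixed as a cost per day of stay saved, although the protocol gives no reason to expect a shorter stay, and the ratio breaks down at or below zero days saved

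*Protocol article*

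**What the plan says.** The Cost-effectiveness analysis section takes two perspectives, hospital and societal. For the hospital it notes that "the surgical treatments to be analyzed do not differ in their DRG-codes", and that for this reason "the costs for the hospital will be estimated based on differences in costs of implants used for the surgery and length of hospital stay". The summary measure follows: "Cost-benefit is then expressed as cost per reduced length of stay". The societal part is a separate cost per QALY.

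On stay itself, the section on the intervention group says "Hospital admission lasting 8-10 days will be necessary". This follows sentences about all patients and both groups. No arm-specific stay, difference or SD is given.

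The Discussion says "In the intervention group, the approach to the spine will be enlarged compared to that of the monosegmental fusion group", that "The longer approach itself could bring about a negative outcome compared to that of regular fusion", and that "topping off devices are quite expensive compared to conventional implants". The section on sample size says "Our target recruitment is 30 patients".

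**The concern.** A ratio per day saved is a useful summary only if days are in fact saved. The article names no mechanism by which adding a flexible system above the fusion would shorten admission. Its intended benefit is protection of the adjacent segment, which is assessed over months and years after discharge. What the article says about the perioperative period (one common admission range, a larger approach, possible muscle damage, blood loss and infection) points to an equal or longer stay rather than a shorter one.

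If the true reduction is near zero, a ratio with that reduction in the denominator takes its sign and size largely from chance. If the hybrid stay is longer, the figure is negative and its ordering is reversed. The article cites the device's high cost as one reason for evaluating it, so a hospital reader may look to this figure and be misled by it.

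**Working it through.** **The plan's own figure.** The article states no number for the hospital ratio. Its only design calculation, a detectable difference of 11.2 on the SF-36 physical score, reproduces (11.23 by the exact t-test with 13 and 14 patients), but it does not bear on this point.

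**Form of the ratio.** Let I be the extra implant cost of the hybrid (positive according to the Discussion, amount not given), c the cost of one bed-day (not given), and R the days saved, control minus hybrid. The costing sentence can be read in two ways:

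- Reading A, stay is not priced into the cost: ratio = I/R.
- Reading B, stay is priced into the cost: ratio = (I − cR)/R = I/R − c.

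Both are undefined at R = 0. For illustration only, assume I = 2000 and c = 500:

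| Days saved R | Reading A | Reading B |
|---|---|---|
| 2 | 1000 | 500 |
| 1 | 2000 | 1500 |
| 0.5 | 4000 | 3500 |
| 0.1 | 20000 | 19500 |
| 0 | undefined | undefined |
| −0.1 | −20000 | −20500 |
| −0.5 | −4000 | −4500 |
| −1 | −2000 | −2500 |
| −2 | −1000 | −1500 |

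A stay 2 days longer thus gives a value nearer zero than a stay 0.1 day longer. Under reading B the ratio is also negative when R exceeds I/c (here 2000/500 = 4 days), where the hybrid is cheaper and shorter. One sign then covers opposite conclusions. Under reading A, with I positive, a negative value can only mean a longer stay.

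**Precision of the denominator.** Stay is measured on the ward, and the primary analysis set includes all randomized patients, so about 15 v 15 of the 30 applies (equal allocation assumed). The SD of stay is an assumption of 1 to 2 days. The difference in means is treated as normal.

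- SE = SD × √(1/15 + 1/15) = SD × 0.365, which is 0.37 days at SD 1 and 0.73 days at SD 2.
- No true difference: P(observed reduction) = 50%.
- True reduction of 0.5 day: P(observed difference in the wrong direction) = Φ(−0.5/SE) = 8.5% at SD 1 and 25% at SD 2.
- Hybrid truly 0.5 day longer: by symmetry, a reduction is observed in 8.5% to 25% of trials.

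At SD 3 the SE is 1.10 days and the wrong-direction probability 32%. With 13 v 14 patients the SE is 0.39 to 0.77 days and the probability 10% to 26% (SD 1 to 2), so the conclusion does not depend on the choice.

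**Spread of the ratio.** A simulation of reading B with the illustrative I and c, 15 per arm and no true difference gave a central 95% range of about −90000 to +86000 at SD 1 and −44000 to +43000 at SD 2.

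**The case against.** Four stronger readings are tempting, and the objections to them are sound.

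- A reader might infer that stay is counted twice and that this alone spoils the ratio. Double counting is only one reading of the costing sentence, which may simply list two inputs that are then combined. Even under reading B, with a clearly positive R, I/R − c is an interpretable net cost per day saved.
- A reader might infer that the plan expects a reduction of zero or below. It states no expected difference. That is an inference from one common range and a Discussion sentence that says only that harm could occur, without mentioning stay.
- A reader might infer that cost is the reason for the trial. The four questions under Objective are clinical and radiographic, and the Discussion calls preventing adjacent segment disease the crucial question. Cost is one motive, and the economic result is an addition.
- A reader might infer that leaving out operating time favours the hybrid. The article says the approach is larger but says nothing about duration, so the omission may favour the hybrid, no more.

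It is also fair to say that any incremental ratio, cost per QALY included, is undefined at zero effect, and that display and interval methods usually belong in the full protocol or analysis plan. That does not remove the point. The article itself fixes this summary measure, and it chose a denominator for which it offers no expected gain. The instability at and below zero holds under both readings.

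**Conclusion.** The point holds in limited form. The hospital result is fixed as a ratio whose denominator the article gives no reason to think positive. The ratio is undefined at zero, unstable near it with about 15 patients per arm, and ordered the wrong way round when the hybrid stay is longer. If stay is also priced into the cost, a negative value can mean either dearer and longer or cheaper and shorter.

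The algebra needs no assumed values. The probabilities (a coin toss with no true difference, 8.5% to 25% wrong direction with a true half-day reduction) rest on the assumed SD of 1 to 2 days. If the hybrid in fact shortened stay clearly, for instance by a full day at SD 1, the ratio would be usable, so the size of the problem depends on a true difference near or below zero.

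This is worth correcting, but it is confined to a secondary economic result.

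**What to change.** In the Cost-effectiveness analysis section, replace the ratio with the mean difference in hospital cost per patient (implant cost plus days of stay × cost per day), with a bootstrap 95% confidence interval. Report the difference in length of stay separately, in days. Since the plan says the two procedures share DRG codes, the cost difference answers the hospital's question directly and stays readable whatever the sign of the stay difference.

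Pricing the surgical duration already recorded under Secondary Outcome Measures (item 8) is an optional addition; it needs one further unit cost.

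The cost is small: a change of wording, a bed-day cost if stay was not already to be priced, a little more analysis, and the loss of a single summary ratio. No new patient data are needed.
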